#### Sociodemographic Questionnaire

This is a simple tool used to collect key personal data from study participants. The information collected includes date of birth (dd/mm/yy), sex (male, female, or intersex), current marital status (married, cohabiting, separated, divorced, single, widowed, and do not know or refuse to answer), level of education (no education, primary education, secondary education, tertiary education, and do not know or refuse), total years of education and current employment status (retired, full-time employment, part-time employment, unemployed, working from home, do not know, and refuse), details of last job, current source of income (work, pension, annuity, help from relatives, social security benefits, other, do not know, and refuse), and possible cohabitants (none, spouse or partner, children, grandchildren, sons-in-law or daughters-in-law, brothers or sisters, mother or father, assistant, others, and refuse to answer).

#### The Short Portable Mental Status Questionnaire or the Pfeiffer Test

This is a tool designed to assess cognitive impairment in older patients [25]. This tool was designed to provide health care professionals working with older patients with an effective and simple method of assessing cognitive impairment. The Short Portable Mental Status Questionnaire is a short questionnaire consisting of 10 questions investigating certain aspects of cognitive ability: 7 on orientation (spatial, temporal, personal, and environmental), 2 on long-term memory (telephone number or address and mother’s maiden name), and 1 on concentration (serial subtraction). Questions should be asked in the order they appear in the protocol, and a score of 0 is assigned for each unanswered or incorrect question, or 1 for each correct answer. The maximum possible score ranges from 0 (indicating maximum cognitive impairment) to 10 (indicating no cognitive impairment). A correction must be applied to the obtained score based on the participant’s level of education: if the number of errors is 0, no correction is made for the patient’s level of education; if the patient’s level of education is less than 8 years, subtract 1 from the raw score; if the patient’s level of education is 8 years, the raw score is not modified; and (4) if the patient’s level of education is more than 8 years, add 1 point to the raw score.

The results are interpreted based on the number of errors made: 0 to 2 errors (cognitive functions intact), 3 to 4 errors (indicative of mild cognitive decline), 5 to 7 errors (indicative of moderate cognitive decline), and 8 to 10 errors (severe cognitive decline).

This quick tool helps to define the presence and intensity (mild, moderate, and severe) of cognitive disorders of organic origin in older patients. It can be used by medical staff and other healthcare professionals in any setting. It can also be used with blind people.

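### The SPMSQ education correction carries error-count signs but is applied to a correct-answer score, so at a corrected cut-off of zero errors it reverses who is admitted with one error

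*Protocol article*

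**What the plan says.** All the scoring text is in the Protocol article, under The Short Portable Mental Status Questionnaire or the Pfeiffer Test.

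- **Item score:** "a score of 0 is assigned for each unanswered or incorrect question, or 1 for each correct answer".
- **Scale:** the total "ranges from 0 (indicating maximum cognitive impairment) to 10 (indicating no cognitive impairment", so higher is better.
- **Correction is mandatory:** "A correction must be applied to the obtained score based on the participant’s level of education".
- **Zero errors:** "if the number of errors is 0, no correction is made for the patient’s level of education".
- **Low schooling:** "level of education is less than 8 years, subtract 1 from the raw score".
- **Exactly 8 years:** "if the patient’s level of education is 8 years, the raw score is not modified".
- **High schooling:** "level of education is more than 8 years, add 1 point to the raw score".
- **Interpretation:** "The results are interpreted based on the number of errors made", with 0 to 2 errors as the intact band and more errors meaning greater decline.

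Two other places give the scale its role. The inclusion criteria (Participants, Textbox 1) require full cognitive abilities, defined as SPMSQ=0. Recruitment (T0) has the researcher administer the scale to confirm that the person qualifies. Neither says whether the value is raw or education-corrected.

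**The concern.** The section changes unit twice. It scores in correct answers, applies the correction to that score, and reads the result in errors. An education correction is ordinarily meant to offset the advantage that schooling gives on the test. Taking a point from a less-schooled person and giving one to a more-schooled person, on a scale where points are good, does the opposite.

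This matters because the scale is an entry screen and not merely a descriptor. The Discussion says the study was restricted to people with full cognitive capacity for safety and data quality, and to keep cognition from confounding the feasibility outcomes. If the corrected value decides entry, the rule as printed selects partly on schooling in an unintended direction. Screeners also cannot apply the inclusion criterion and the scoring section together without guessing the unit, because 0 is the best possible result in errors and the worst in correct answers.

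**Working it through.** The article gives no figure to reproduce, so the check is to follow the printed rule and compare it with the same signs placed on the error count.

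**Inputs (all from the SPMSQ section, except the cut-off from Textbox 1)**

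- e = raw number of errors, 0 to 10; raw score c = 10 − e.
- a = −1 below 8 years of schooling, 0 at 8 years, +1 above 8 years; a = 0 whenever e = 0.
- Cut-off: SPMSQ=0. On the correct-answer scale 0 is maximum impairment, which contradicts the criterion's requirement of full abilities. The cut-off can therefore only mean zero errors.

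**Formulas**

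- As printed (correction on correct answers): corrected score = c + a, so corrected errors = 10 − (10 − e + a) = e − a.
- Same signs on the error count: corrected errors = e + a.
- Difference between the two: (e − a) − (e + a) = −2a, which is 2 errors in size for anyone with at least one error and schooling other than 8 years.

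**Effect on the schooling gap.** Take two people with the same raw errors (1 to 9), one below and one above 8 years. As printed, the less-schooled person ends with (e + 1) − (e − 1) = 2 more corrected errors. On the error count, that person ends with (e − 1) − (e + 1) = −2, that is, 2 fewer.

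**Effect at the cut-off**

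| Raw errors | Schooling | As printed: corrected errors | On errors: corrected errors | As printed | On errors |
|---|---|---|---|---|---|
| 0 | any | 0 | 0 | admitted | admitted |
| 1 | under 8 years | 10 − (9 − 1) = 2 | 1 − 1 = 0 | rejected | admitted |
| 1 | 8 years | 10 − 9 = 1 | 1 | rejected | rejected |
| 1 | over 8 years | 10 − (9 + 1) = 0 | 1 + 1 = 2 | admitted | rejected |
| 2 or more | any | at least 1 | at least 1 | rejected | rejected |

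The algebra confirms that nothing else moves. With e at least 1, corrected errors reach zero as printed only if e = a, so e = 1 with schooling over 8 years. On the error count they reach zero only if e = −a, so e = 1 with schooling under 8 years.

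**If the cut-off is raw errors,** only e = 0 qualifies, no correction applies to those people, and eligibility is the same under both versions.

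**Number affected.** This would need the joint distribution of raw errors and schooling among people screened. The article gives neither, so no count or percentage can be derived.

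**The case against.** The strongest reply is that the article never says the corrected value decides entry. Textbox 1 gives only SPMSQ=0, and the interpretation sentence can be read as referring to raw errors. On that reading the correction never touches eligibility. This stands as a limit on the consequence. It does not rescue the rule, because the same section makes the correction compulsory and nothing designates the cut-off as raw.

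A second reply is that the article may have mis-transcribed a form that is used correctly on site. That is possible: neither the form nor the cited source is shown. It is a reason to check the form before changing anything.

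Three stronger readings are tempting, and the article supports none of them.

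- *People with mild decline are enrolled.* A reader might infer this from the severity bands, since the correction can move someone across the 2-error boundary. But the entry criterion is 0, not the intact band. The only person admitted through the printed rule has 1 raw error and more than 8 years of schooling. Even with the correction on errors, that person has 2 corrected errors and stays in the intact band.
- *Every corrected score is wrong.* People with no errors, and people with exactly 8 years of schooling, get the same result either way.
- *Usability and satisfaction results are biased upwards.* A link between schooling and these ratings is plausible, but the article gives no figure for it, nor for the number of people affected. The same screen applies to both robots, and the outcomes are to be interpreted descriptively.

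**Conclusion.** The contradiction is certain and rests on one section: a higher-is-better score receives a correction whose signs offset schooling only on a lower-is-better count, and the result is then read in that other unit. The one premise from outside the text is that an education correction is meant to offset schooling. The article's own use of errors for both the zero-error exemption and the interpretation points the same way.

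The consequence is conditional and narrow. If the SPMSQ=0 criterion uses the corrected result, eligibility is reversed for people with exactly 1 raw error and schooling other than 8 years: those above 8 years enter and those below do not. If the criterion uses raw errors, enrolment is unchanged. The sample size and the planned analyses are not affected numerically; what may be affected is who was enrolled and how the population is described. The size of that effect is unknown from the article.

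**What to change.** 1. Check the scoring form actually used at screening, to establish whether the fault is in the article or in practice.
2. Reconcile Textbox 1 with the SPMSQ section by using one unit throughout. Either count errors and apply the stated signs to the error count, or keep correct answers and reverse both signs. Interpret the result, and state the cut-off, in that same unit.
3. State whether the inclusion cut-off is the raw or the corrected value.
4. Recompute the corrected value for everyone screened, and report how many were enrolled or excluded through the inverted rule. Total years of education is already an item of the Sociodemographic Questionnaire. The recount also needs the raw error count of people who were turned away, and it is an assumption that this was kept.

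The wording change costs almost nothing. The recount is time-limited, because Data Management provides for screening data to be erased when the project ends. People already turned away cannot be recovered. Some people already enrolled may prove not to meet the reconciled criterion; they should be counted and reported openly.

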#### Health Status Questionnaire

As well as asking for the participant’s age, the questionnaire uses dichotomous questions and scales ranging from 1 to 5 to assess their visual and hearing abilities. For example, it asks whether they can read a book or watch television with adequate lighting, with or without lenses, and whether they can follow a conversation or use the telephone, even with a hearing aid. The user will assess their own sense of sight and hearing, rather than the researcher.

#### SUS Tool

The SUS is a reliable tool for measuring usability. It consists of a 10-item questionnaire in which respondents are asked to indicate their level of agreement or disagreement with a series of statements using a 5-point scale ranging from “Strongly Agree” to “Strongly Disagree.” The SUS allows for the evaluation of a wide variety of products and services, including hardware, software, mobile devices, websites, and applications. The SUS is easy to administer and can produce reliable results in small samples, effectively distinguishing between usable and unusable systems.

#### Customer Satisfaction Questionnaire

This tool is designed to assess user satisfaction after using the 2 robotic platforms. Satisfaction is assessed by quantifying various variables, such as: the attention received from the robot in terms of accuracy and courtesy (scoring from 1=“not at all satisfied” to 7=“very satisfied”), the clarity and completeness of the information received (scoring from 1=“not at all satisfied” to 7=“very satisfied”), respect for personal privacy (scoring from 1=“not at all satisfied” to 7=“very satisfied”), overall satisfaction with the service offered (scoring from 1=“not at all satisfied” to 7=“very satisfied”), and whether they would recommend our service to others (scoring from 1=“absolutely not” to 7=“definitely yes”).

#### Godspeed

It allows users to quantify certain characteristics of the platform perceived during use, using a score ranging from 1 to 5 for each item. In particular, it refers to anthropomorphism, animation, friendliness, intelligence, and perceived safety.

### Procedure

#### Recruitment (T0)

The robots will be placed in a dedicated area (a closed box) at the hospital entrance. Only one user will be allowed in at a time. A researcher will stop users at the hospital entrance and invite them to participate in the study. Participants must confirm their willingness to participate in writing. After signing the consent forms, the technology will be assigned to them in a randomized alternating manner (ABAB) according to the order of inclusion of participants. Then, the researcher will collect general information about the patient and administer the cognitive scale to verify that the user meets the inclusion criteria.

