**Figure 1. F1:**
[figure not shown]
The study design. SPMSQ: Short Portable Mental Status Questionnaire; SUS: system usability scale.

A total of 200 older adults will be recruited for this single-center feasibility pilot with a pragmatic quasi-experimental design. For logistical reasons, entire days will be dedicated to either Nao or Pepper. Participants will be equally allocated to interact with Nao or Pepper based on alternating study days and a predetermined quota system: once 100 participants have interacted with one robot, all subsequent participants will use the other robot until a total of 100 participants are reached for each. The allocation schedule will be predetermined and documented to ensure transparency.

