### Statistical Analysis

Sample size determination followed feasibility study conventions rather than power calculations for confirmatory testing. Previous studies evaluating patient satisfaction with novel health care service innovations enrolled 124 to 177 participants [26,27]. To provide robust descriptive data across both feasibility indicators (recruitment, completion, and acceptability) and the balanced quasi-experimental design (n=100 per robot), the HOSPER study targets 200 participants (100 Nao and 100 Pepper). This sample size supports reliable estimation of prevalence estimates (eg, satisfaction proportions) while remaining practical for a single-center pilot. In the case that the statistical analysis reveals a positive trend, a new protocol will be proposed with the aim of conducting a trial.

Continuous variables will be reported as mean and SD, or median and IQR, depending on their distribution (as assessed using the Kolmogorov-Smirnov). Categorical variables will be expressed as absolute numbers and percentages.

Descriptive statistical analysis will be conducted on quantitative data with SPSS (Statistical Package for the Social Sciences; IBM Corp) and RStudio (Posit PBC). The robot’s logs (computer records) will be extracted in order to make a technical assessment of the objective parameters of HRI: dialogue comprehension ability, questions asked, answers given, dialogue duration, and so on.

Moreover, HRI will be analyzed using the Noldus system, considered the gold standard for behavioral analysis. Specifically, FaceReader and Observer (Noldus Information Technology) will be used to analyze audio-video recording of interactions. FaceReader uses facial analysis to identify the Ekman 7 emotions (neutrality, happiness, anger, sadness, disgust, fear, and surprise) in real-time [28] and summarize emotional valence distributions. Instead, the Observer enables the analysis of the interaction quantitatively and qualitatively by manually inserting labels to code the user’s emotional state and behaviors. Results will describe emotional and behavioral patterns during robot interactions to complement self-reported questionnaires. These analyses can be integrated and stacked with the Noldus software, enabling correlations to be found between the robot’s actions and the user’s behavior. This observational approach is useful for describing the dynamics of interaction and assessing the user’s experience.

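### The protocol gives two incompatible rules for assigning Nao or Pepper, calls a deterministic sequence randomized, and under the day-based rule its quota usually ends recruitment on one robot

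*Protocol article*

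**What the plan says.** Two sections of the protocol article describe how a participant comes to meet Nao or Pepper.

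- **Study Design, text under Figure 1.** The study is a "single-center feasibility pilot with a pragmatic quasi-experimental design". For logistical reasons "entire days will be dedicated to either Nao or Pepper". Allocation is "based on alternating study days and a predetermined quota system", and "once 100 participants have interacted with one robot, all subsequent participants will use the other robot" until that robot also has 100. The schedule is to be fixed in advance and documented.
- **Recruitment (T0).** After consent, "the technology will be assigned to them in a randomized alternating manner (ABAB) according to the order of inclusion of participants". The eligibility check comes next: "Then, the researcher will collect general information about the patient and administer the cognitive scale to verify that the user meets the inclusion criteria".

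Statistical Analysis plans t, Mann-Whitney or Fisher tests of Nao against Pepper. It labels them descriptive and rules out causal conclusions. Exploratory regression on possible confounders is allowed, but study day and calendar period are not named among them.

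**The concern.** The allocation unit is a study day in one section and a participant in the other. Each rule is stated explicitly, so this is a conflict and not a detail shortened for the article. The word *randomized* also appears in only one of the two, attached to a sequence that involves no chance.

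What is at stake is how the Nao-Pepper comparison can be read. Results announces a direct comparison of the two systems on the SUS, and the sample size is built on balanced groups of 100. Even a descriptive comparison needs a true account of who received which robot and why. If days are the unit, the quota adds a second problem: once one robot is full, everyone recruited later sees the other robot, with no concurrent comparator.

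**Working it through.** **1. The two rules side by side**

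| | Study Design | Recruitment (T0) |
|---|---|---|
| Unit | study day | participant |
| Sequence | alternating days, then quota switch | ABAB by order of inclusion |
| Label | quasi-experimental | randomized |
| Next two people on the same day | same robot (unless the quota is reached between them) | different robots |

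The last row shows that the rules cannot both hold. No other section reconciles them. Both sequences are deterministic, so the researcher who approaches visitors can predict the next assignment under either rule.

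**2. The plan's own figure.** 100 + 100 = 200, which agrees with the stated total. No alpha, power, effect size or SD is given, so there is no further sample size figure to reproduce.

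**3. Single-robot tail under the day rule.** Let the tail be 100 minus the count on the slower robot when the other reaches 100. Daily intake is not in the document and is assumed here. Alternating days with a stop at 100 per robot were simulated, 4,000 runs per scenario.

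| Assumed intake | Mean tail (of 100) | 95th percentile |
|---|---|---|
| Equal, Poisson, 1 to 8 per day | 11 to 12 | 26 to 28 |
| Equal, overdispersed (gamma variance 0.5), 1 to 8 per day | 13 to 23 | 31 to 53 |
| One robot's days 1.25 times faster | 22 | 40 |
| 1.5 times faster | 34 | 51 |
| 2 times faster | 51 | 65 |

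Two hand checks agree with these results:

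- *Equal intake.* If each arrival is equally likely to fall on either robot's day, the expected tail is 2n × C(2n, n)/2^(2n). With n = 100 the binomial term is about 1/√(100π) = 0.0564, and 200 × 0.0564 = 11.3.
- *Unequal intake with ratio r.* The tail is about 100(1 − 1/r), which gives 20, 33 and 50 for r = 1.25, 1.5 and 2.

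In the equal-intake scenarios the tail lasts about 2 to 14 study days on average, depending on the daily count.

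**4. Effect on the comparison.** If the outcome shifts by D during the tail, the robot difference is biased by about (tail/100) × D. That is 0.11 D for a tail of 11 and 0.23 D for a tail of 23. The documents give no value for D.

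**5. Tail under the ABAB rule.** If alternation runs over eligible participants, the counts never differ by more than 1, so the tail is at most 1. Recruitment (T0) places assignment before the cognitive screen. If slots lost to screen failure are not reused, the mean tail is about 4, 7 or 8 at assumed failure rates of 10%, 30% or 50%.

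**6. Cost of slightly unequal groups.** The variance of a difference relative to 100/100 is (1/n1 + 1/n2)/(2/100). For 90/110 this is 0.020202/0.02 = 1.010. For 95/105 it is 0.020050/0.02 = 1.0025.

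**The case against.** The strongest defence is that little depends on the robot contrast. The primary end point is perceived quality of the service, summarized descriptively. The three feasibility thresholds (70%, 70% and 80%) concern agreement to participate, completion and data completeness, and none compares robots. Statistical Analysis disclaims inference and causal conclusions, and Study Design already says quasi-experimental. All of this stands and limits the severity. It does not remove the contradiction or make the word *randomized* correct.

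It is also fair that the tail belongs to only one of the two rules, and that robots alternate by day until one is full. Most recruitment is therefore concurrent in the equal-intake scenarios. The quota has a purpose too: it secures the planned 100 per robot.

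A reader might go further, but the documents do not support these inferences:

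- *Robot is wholly confounded with calendar time.* Only the tail lacks a concurrent comparator.
- *Each robot is tied to fixed weekdays or clinics.* This needs an even number of study days per week, which is not stated; with five, strict alternation swaps weekdays each week.
- *Software changed during the study.* The Equipment section describes fixed, identical scripts, and technical notes are meant for future updates.
- *Visitors know the robot before consenting.* The robots stand in a closed box.
- *The comparison has no defined analysis.* The tests are named. Whether to allow for clustering by day is a fair question, but that is commonly left to an analysis plan.

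**Conclusion.** The allocation rule is wrong as written. Study Design and Recruitment (T0) cannot both be followed, and *randomized* is incorrect under either. This rests on the text alone.

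The quota point is conditional. If the day rule governs, on average about 11 to 23 of the later arm's 100 participants have no concurrent comparator. The average rises to about 34 or 51 if one robot's days recruit 1.5 or 2 times faster. These figures depend on assumed daily intake. The resulting confounding with calendar time is partial, and its size depends on an unknown period shift. Under ABAB among eligible participants it is negligible.

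The effect is confined to the secondary, descriptive Nao-Pepper comparison. The primary end point and the feasibility criteria are untouched. The point should be fixed, but it is not critical to the study.

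**What to change.** 1. State one allocation unit in both sections. If logistics require whole days, keep the day rule and delete the ABAB sentence together with *randomized* from Recruitment (T0). Alternatively, make the word true by drawing the robot order at random within each consecutive pair of study days from a list prepared in advance.
2. If the day rule with quota was used, say so in the report, flag the participants recruited after the first robot closed, and repeat the Nao-Pepper comparison without them.
3. If recruitment is still open, an option is to drop the quota switch and keep both robots rotating to 200 in total.

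The first correction costs wording and, if days are drawn at random, a short list. The second needs only the date and robot for each participant and one repeated analysis. The third gives up exact balance, at about 1% more variance for a 90/110 split. Because ethics approval and the start of recruitment have already passed, a change to the allocation itself may need an amendment; correcting the description and reporting the tail does not alter conduct.
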